#### Data collection

Data are collected using a standard case report form. Data are de-identified before being entered into the database. The study site is regularly monitored and the database checked to ensure the accuracy of data collected. The data management, monitoring, and reporting of this study will comply with the International Conference on Harmonisation Good Clinical Practice (ICH-GCP) guidelines.

#### Data analysis plan

Data analysis and reporting will be conducted in accordance with the Consolidated Standards of Reporting Trials (CONSORT) 2010 Statement, as shown in our flow chart (Fig. 1), including the number of eligible participants and the number lost to follow up for various reasons. Data analysts will be blinded to the participants’ assigned interventions. Unblinding of a participant’s allocated intervention during the trial is permissible after blind verification and a submission of data locking proof by statistical analyst.

**Fig. 1 Fig1:**
[figure not shown]
Flowchart of this study

Intention to treat, which is based on the initial treatment intent, will be used as a foundation in our analysis. Participants who begin the allocated treatment are part of the trial, whether they finish it or not. The characteristics at baseline will be compared between the control and intervention groups. Continuous data will be summarized by the mean and standard deviation and the Wilcoxon rank sum test will be used to identify differences in baseline characteristic between the two groups. Categorical data will be described by number and percentage, using the Pearson chi-square test to compare data from the two groups.

The primary outcome measure is the difference in the recurrence rate between group A and group B after 3 years of follow up, which will be analyzed by the Pearson chi-square test. For efficacy parameters, such as the score for pelvic pain and dysmenorrhea, menstrual blood loss, and the size of the uterus and the lesion, will be analyzed using generalized estimating equations (GEE) or mixed effects model repeated measures (MMRM) to account for correlation among these observations at different follow-up points.

The variables from secondary outcomes, including scores on the SF-36 and the FSFI, the pregnancy rate, and pregnancy outcomes, are calculated during 36 months of follow up using GEE or MMRM analysis to compare groups A and B to identify differences between groups at different time points. The number of participants with adverse events (AE) or serious adverse events (SAE) will be calculated in each arm and taken into final statistical testing.

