## Method/design

Participants (*n* = 308) who have undergone complete excision of focal adenomyosis will be randomly assigned 1:1 to the treatment group (triptorelin acetate) or the control group. Patients will be recruited at 10 hospitals across mid-west China. All research units have been approved by the ethics committees. Every patient will sign an informed consent form prior to this study. This report follows the Standard Protocol Items: Recommendations for Interventional Trials (SPIRIT) guideline (Additional file 1).

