### Screening and enrollment

Previous medical history and current medication status are reviewed in the standardized case report forms. A physical examination and imaging such as two/three-dimensional color doppler ultrasonography (2D/3D-CDUS) or magnetic resonance imaging (MRI) are performed. Laboratory measurements include measurement of serum follicle-stimulating hormone (FSH), estradiol (E2), anti-Muellerian hormone (AMH), cancer antigen 125 (CA125), and safety assays including routine analysis of blood, urine, liver function, renal function, hepatitis virus, HIV, syphilis, and coagulation; electrocardiogram (ECG) and radiography are performed in the local departments at the study sites. Either laparoscopy or transabdominal surgery is performed to completely remove all clinically recognizable lesions in patients who are suspected to have focal adenomyosis.

Written informed consent will be obtained from the patients after surgery. Quality of life, degree of pain, and menstrual volume will be recorded using the Short Form (36) Health Survey (SF-36), Female Sexual Function Index (FSFI), pictorial blood loss assessment chart (PBAC) score, visual analogue scale (VAS) and numeric rating scale (NRS) after confirming by histologic assessment. A schedule of enrollment, interventions, and assessment is provided Table 1.

**Table 1 Tab1:** Schedule of screening, enrollment and assessment

Evaluation	Screening	Enrollment	Time of follow up after surgery (month)						
			3	6	12	18	24	30	36
Written consent		√							
Inclusion/exclusion criteria		√							
Medical history	√								
Physical exam	√								
Safety test (preoperative examination)	√								
2D/3D-CDUS/MRI	√		√	√	√	√	√	√	√
FSH, E_2_, AMH, CA125	√		√	√	√	√	√	√	√
Side effects			√	√	√	√	√	√	√
VAS and NRS		√	√	√	√	√	√	√	√
SF-36 and FSFI		√	√	√	√	√	√	√	√
PBAC score		√	√	√	√	√	√	√	√

*2D/3D-CDUS/MRI* two/three-dimensional color doppler ultrasonography/magnetic resonance imaging, *FSH* follicle stimulating hormone, *E*_*2*_ estradiol, *AMH* anti-Muellerian hormone, *CA125* cancer antigen 125, *VAS* visual analogue scale, *NRS* numeric rating scale, *SF-36* Short Form-36 Health Survey, *FSFI* Female Sexual Function index, *PBAC* pictorial blood loss assessment chart

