### Interventions

Eligible participants are assigned by simple randomization in a 1:1 ratio to a group receiving surgery only (group A) or to a group receiving surgery plus GnRH agonists (group B). The GnRH agonist is administered in the intervention group as a 3.75 mg intramuscular injection (Diphereline, Ipsen, France) on the first day of menstruation after surgery, then once every 4 weeks for six courses. The signs and symptoms of hypoestrogenism, including hot flushes, night sweats, sleep disorders, abnormal emotions and osteoporosis, could be caused by the GnRH agonist; these should be carefully evaluated and participants could be treated with tibolone 1.25 mg per day as add-back therapy to maintain serum estradiol at 30–50 pg/ml [17].

The intervention will be discontinued or modified if an intolerable adverse reaction occurs in group B. Color doppler ultrasonography and a steroid hormone test on the 3rd and 6th month after conservative surgery can help to monitor adherence. During the trial, other medications, such as steroid hormone or herbal medicine, or another intervention, such as levonorgestrel-releasing intrauterine system (LNG-IUS) will be prohibited.

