### Randomization

Eligible participants are assigned by simple randomization in a 1:1 ratio to one of two groups. The sequence of randomization has been set up by biostatisticians in the data coordination center using Microsoft Excel and the “RAND ()” function. The original sequence is safely kept by the staff in the data coordination center, and it has been put into the online central randomization system by these staff members, who are not involved in enrolling subjects. The sequence is not accessible to any investigators or study coordinators. If a subject fulfills the enrollment criteria, the authorized study coordinator will obtain the assignment for her. After randomization, both subjects and investigators are informed about the assignments.

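### The protocol names intention to treat but defines membership by beginning the allocated treatment; read as written, only triptorelin-arm women could be excluded

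*Protocol article*

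**What the plan says.** The Data analysis plan (paragraph after Fig. 1) opens with the principle: "Intention to treat, which is based on the initial treatment intent, will be used as a foundation in our analysis". The next sentence gives the only rule on who counts: "Participants who begin the allocated treatment are part of the trial, whether they finish it or not". The primary comparison, recurrence over 3 years in group A against group B by Pearson chi-square test, follows in the next paragraph.

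Four other places determine how that rule works in this trial:

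- Method/design: the women randomised are those "who have undergone complete excision of focal adenomyosis will be randomly assigned 1:1 to the treatment group (triptorelin acetate) or the control group".
- Screening and enrollment: "Written informed consent will be obtained from the patients after surgery".
- Interventions: group A receives surgery only. Group B also receives the GnRH agonist, first given "on the first day of menstruation after surgery, then once every 4 weeks for six courses".
- Randomization: "After randomization, both subjects and investigators are informed about the assignments".

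**The concern.** Under intention to treat, a woman enters the analysis by being randomised. Here the stated rule ties entry to starting treatment. The two agree only if every randomised woman starts, or if starting is defined so that nobody can fail it.

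The design makes the difference one-sided. Nothing remains for a group A woman to begin after randomisation, whereas a group B woman still has a first injection to come. If the rule is applied literally, a group B woman who learns her allocation, declines the injection and stays in follow-up would leave the analysis, while her counterpart in group A stays. The primary comparison would then set a selected group B against a complete group A. The planned chi-square test is unadjusted, so it would not correct for that selection.

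**Working it through.** **1. Who can fail the rule.** The rule rests on no figure in the plan, so there is none to reproduce. The check is to set the sections side by side.

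| | Group A | Group B |
|---|---|---|
| Surgery done before randomisation | yes | yes |
| Treatment still to begin after randomisation | none | first injection, at first menstruation after surgery |
| Allocation known to woman and investigator | yes | yes |
| Can be a non-starter | no | yes |

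No other sentence defines the analysis set or says that all randomised women are analysed as assigned.

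**2. Effect on the estimate if the planned effect is real.**

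Inputs from Sample size calculation: 49% relapse with surgery alone, 28.1% with surgery plus agonist, 308 women in total (about 154 per arm). Assumptions, not in the document: a share f = 5–10% of group B never starts (0.05 × 154 ≈ 8 to 0.10 × 154 ≈ 15 women), starters relapse at 28.1%, and non-starters relapse at r = 49%.

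Group B rate as randomised = (1 − f) × 0.281 + f × r. The starters set reports 0.281, so the overstatement is f × (r − 0.281).

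- f = 0.05: 0.95 × 0.281 + 0.05 × 0.49 = 0.2670 + 0.0245 = 0.291. Overstatement 0.05 × 0.209 = 1.0 point.
- f = 0.10: 0.90 × 0.281 + 0.10 × 0.49 = 0.2529 + 0.0490 = 0.302. Overstatement 0.10 × 0.209 = 2.1 points.

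The planned difference is 49 − 28.1 = 20.9 points. The sign of f × (r − 0.281) turns negative when non-starters relapse less often than starters.

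**3. Effect on the test if the drug does nothing.** Take 49% relapse in both arms as randomised. If non-starters relapse at q, the rate among group B starters is (0.49 − f × q)/(1 − f), and the false difference d is 0.49 minus that. Type I error is approximated by Φ((d − 1.96·SE₀)/SE₁) + Φ((−d − 1.96·SE₀)/SE₁), where SE₀ is the pooled and SE₁ the unpooled standard error. There are 154 women in group A and 146 (f = 5%) or 139 (f = 10%) in group B. Worked case, f = 0.10 and q = 0.30: (0.49 − 0.03)/0.90 = 0.511, so d = −2.1 points.

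| Assumed q | f = 5%: d (type I error) | f = 10%: d (type I error) |
|---|---|---|
| 30% | −1.0 (5.3%) | −2.1 (6.5%) |
| 49% | 0.0 (5.0%) | 0.0 (5.0%) |
| 70% | +1.1 (5.4%) | +2.3 (6.8%) |
| 90% | +2.2 (6.6%) | +4.6 (12.2%) |

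Positive values favour triptorelin. The bias can go either way, and it vanishes when non-starters relapse like the rest.

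**4. Power if all randomised women are kept.** With 139 per group, two-sided alpha 0.05, 49% in group A and the group B rates from step 2, the normal approximation gives 92.8% (f = 5%) and 89.8% (f = 10%). Both exceed the 85% target.

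**The case against.** The strongest reply is that the sentence only adds protection. It says that starters stay in even if they stop; it does not say that only starters are in. The sentence before it invokes initial treatment intent, and the same section commits to CONSORT 2010. On that reading the authors meant full intention to treat. This is plausible, and it stands as a limit on the finding. It does not make the text adequate: the rule is silent on the group that separates intention to treat from a starters set, and nothing else in the article fills the gap.

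Second, surgery is part of both regimens under Interventions, so every randomised woman might be said to have begun. That reading is available, but less natural. Surgery precedes randomisation and is common to both arms, so what is allocated is triptorelin or no triptorelin, and Method/design labels the treatment group by the drug. On this second reading the rule excludes nobody and should simply say so.

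Third, precise analysis sets are often left to a full protocol or SAP. That would answer silence. Here the article states a rule, and the rule sits badly with its own label.

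A reader might go further and infer that the plan does exclude non-starters and so biases the result towards triptorelin. The document does not support that. It gives no non-start rate, no relapse rate in non-starters and no interval between allocation and first injection, so a long window for non-starting cannot be assumed. Women lost before the injection are largely a missing-outcome problem that can affect either arm. The argument applies cleanly only to group B women who do not start but remain in follow-up.

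**Conclusion.** The point holds as a stated rule in conflict with its label. Read as written, the set that governs the primary comparison is a starters set, and exclusion could occur in group B only, after open-label allocation. It is not established that the authors intend this, or that the randomised comparison will in fact be broken.

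The size and direction of bias are unknown. The illustrative 1.0–2.1 points out of 20.9 rests on assumed non-start rates of 5–10% and on non-starters relapsing at the control rate. With no drug effect, the assumed ranges give false differences from −2.1 to +4.6 points. The 12.2% type I error belongs to the extreme corner (10% non-starters, 90% of them relapsing) and should not be read as an expected value. The correction is still needed, because the sentence decides who enters the primary analysis and can be applied in two ways once allocations are known.

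**What to change.** Replace the membership sentence with: *All randomised participants are analysed in the group to which they were assigned, whether or not they begin or complete the assigned treatment.* If a starters-only set is wanted, define it separately and label it supportive.

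The cost is one sentence. Keeping non-starters may dilute the effect estimate slightly; in the illustration of step 2, the difference falls from 20.9 to 19.9 (49 − 29.1) or 18.8 (49 − 30.2) points, with power still above target. The change does not supply outcomes for women lost early in either arm, so missing outcomes need their own handling.

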### Adenomyomectomy

Laparotomy, hysteroscopy, or laparoscopy are performed in this study. During the laparoscopy, patients are in the lithotomy position under general anesthesia with endotracheal intubation. After sterilization, a pneumoperitoneum is created using carbon dioxide gas at 13 mmHg (Karl Storz GmbH & Co. KG, Tuttlingen, Germany). Surgery is performed using four surgical trocars. The supine position and a median incision are suitable for laparotomy. Hysteroscopic surgery is conducted for type 0 or type 1 adenomyoma (Karl Storz GmbH & Co. KG, Tuttlingen, Germany). The surgical approach is adenomyomectomy. The principles of these surgical options include complete removal of clinically visible lesions, maintaining the integrity of the uterine wall, and retaining the integrity of the uterine cavity as far as possible. The duration of surgery, size of the focus, blood loss, and the integrity of the uterine cavity should be recorded.

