### Data analysis

#### Sample size calculation

Sample size was determined based on data from a prospective study demonstrating a relapse rate of about 49% in the group that received surgery alone and 28.1% in the group that received surgery and GnRH agonist treatment [7]. A two-tailed test with alpha set at 0.05 and 85% power is used to detect a minimum clinically meaningful difference between control and intervention groups. The minimal sample size is calculated as 139 participants in each group. In consideration of a dropout rate of 10%, we will recruit 308 participants in total.

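### The primary relapse comparison is fixed as an unadjusted chi-square; the test is valid, but prespecified adjustment for a few collected baseline variables would gain modest precision

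*Protocol article*

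**What the plan says.** **Primary analysis.** The Data analysis plan defines it in one sentence: "The primary outcome measure is the difference in the recurrence rate between group A and group B after 3 years of follow up". The closing clause of that sentence fixes the method for this comparison: "which will be analyzed by the Pearson chi-square test". It names no covariate, stratum or adjusted estimate.

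**Allocation.** The Randomization section states: "Eligible participants are assigned by simple randomization in a 1:1 ratio to one of two groups". The Interventions section says the same. Neither mentions stratification. The Method/design section states: "Patients will be recruited at 10 hospitals across mid-west China".

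**Baseline data.** Focus size is among the operative items to be recorded (Adenomyomectomy section: "The duration of surgery, size of the focus, blood loss, and the integrity of the uterine cavity should be recorded"). Age is an eligibility criterion. Table 1 places the pain scores and the PBAC score at enrolment, and imaging, hormones and CA125 at screening. Women are randomised after excision (Method/design), so operative findings can serve as pre-randomisation covariates.

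**Use of those data.** The Data analysis plan says: "The characteristics at baseline will be compared between the control and intervention groups", by Wilcoxon or chi-square test. GEE or MMRM is named for pain, bleeding, lesion size and quality of life, again without covariates.

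**The concern.** Simple randomisation balances baseline variables only on average. If some of them predict relapse, an unadjusted comparison has two limits. The variation they explain stays in the error, and any chance imbalance in this particular trial stays in the estimate.

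The Background gives some reason to expect predictors. It links the varying relapse rates after conservative surgery to residual lesion and a poorly defined boundary with normal tissue. Lesion size is therefore a plausible predictor, although the article gives no prognostic strengths.

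Testing baseline differences does not help, because it changes nothing in the primary estimate. If an imbalance does appear, the article gives no rule for what follows, so an adjusted result produced then would rest on covariates chosen after the fact. At stake are some precision and a cleaner prespecified estimate, not the validity of the trial.

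**Working it through.** **Inputs from the article.** Relapse of 49% and 28.1%, two-sided alpha 0.05, power 85%, 139 per group, 10% dropout, 308 in total (Sample size calculation); 10 hospitals; three surgical routes; simple 1:1 allocation. Prognostic strengths and equal hospital sizes are assumptions.

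**Step 1. The plan's own figure.** Pooled two-proportion formula, with p̄ = (0.49 + 0.281)/2 = 0.3855:

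n = [1.960·√(2·0.3855·0.6145) + 1.036·√(0.49·0.51 + 0.281·0.719)]² / 0.209² ≈ 96 per group.

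The stated 139 is not reproduced at 85% power. It corresponds to about 95% (pooled formula 138, arcsine 139), and power at 139 per group is 95.1%. That is a separate matter. It is relevant here because it leaves little room for adjustment to add power at the stated rates.

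**Step 2. Power if the effect is smaller.** Control rate 49%, 139 per group:

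| Treated rate | Power |
|---|---|
| 28.1% | 95% |
| 31.5% | 85% |
| 33% | 78% |
| 35% | 66% |

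**Step 3. What adjustment gains.** Simulation of 3,000 trials per setting, with simple randomisation, 10 hospitals, three routes and one continuous covariate. The chi-square was compared with a logistic Wald test adjusted for nine hospital indicators, route and the covariate. This is a fuller model than the one recommended below. The 192 analysed are the 2 × 96 from step 1, which give 85% power at the stated rates.

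| Assumed log-odds effects (hospital SD / route ± / covariate per SD) | Power at 278, chi-square v adjusted | Power at 192, chi-square v adjusted |
|---|---|---|
| 0 / 0 / 0 | 94.8% v 94.4% | 84.6% v 83.3% |
| 0.3 / 0.3 / 0.3 | 94.8% v 95.1% | 84.7% v 85.7% |
| 0.5 / 0.5 / 0.5 | 95.3% v 96.5% | 84.7% v 87.3% |
| 0.5 / 0.5 / 1.0 | 95.2% v 97.8% | 84.7% v 90.3% |

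The change is about 0 to +3 points at 278 and −1 to +6 at 192. Simulation error is about √(0.95·0.05/3000) = 0.4 points near 95% power and √(0.85·0.15/3000) = 0.7 points near 85%. Type I error is 4.5–5.4% for the chi-square and 5.0–6.6% for this fuller adjusted test.

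A model with few covariates and no full set of hospital indicators stays at about the nominal level. It gains roughly 1 to 4 points when power is near 85% and the covariates are prognostic, and loses almost nothing when they are not.

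**Step 4. Size of chance imbalance.** With 31 women per hospital (assumed), the probability of a 20 v 11 split or worse is 0.150, and for at least one of 10 hospitals it is 1 − (1 − 0.150)¹⁰ = 80%. To turn this into an effect on the estimate, suppose that hospital's relapse rate is 20 points above the rest (assumed). The shift is (20 − 11)/154 × 20 = 1.2 points. The planned difference is 49 − 28.1 = 20.9 points, and its standard error at 139 per group is √[(0.49·0.51 + 0.281·0.719)/139] = 5.7 points.

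**The case against.** The strongest reply is that nothing here is an error. Stratified allocation would oblige the analysis to carry the strata; simple allocation creates no such duty. The unadjusted chi-square matches the design and keeps its level in every simulated setting. All of this stands. A reader might infer that simple randomisation makes the test wrong or biased, and the documents do not support that: chance imbalance is already part of the test's sampling error.

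A reader might also take the 80% figure, or the 28% chance that the arms differ by 20 or more of 308 women, as a measure of damage. Neither is one. Step 4 puts the shift from one such hospital at about 1.2 points. Adjustment does not alter arm sizes, and a 164 v 144 split keeps 4·164·144/308² = 99.6% of the efficiency of equal arms.

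Three further limits stand:

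- **Route and hospital.** Three routes are used ("Laparotomy, hysteroscopy, or laparoscopy are performed in this study"), but route is not among the operative items listed for recording. The Background does not name hospital, surgeon or route as causes of relapse, and the trial requires complete excision in all women.
- **Cost.** Adjustment is not free. Unless sites are pooled, a model with arm, nine hospital indicators, two for route, size and age has 14 terms for about 139 × (0.49 + 0.281) = 107 expected relapses, roughly 8 per term.
- **Scope.** The statistical analysis plan is not shown and may hold adjusted supportive analyses. The point therefore concerns only the primary test that the article states.

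The objection fails in one respect. The article does not leave the primary method open; it names an unadjusted one. A better-chosen version is available at almost no cost, from data already collected.

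**Conclusion.** The point holds as a modest improvement in precision and in robustness to chance imbalance, not as a flaw in validity. The stated primary test is valid but uses none of the baseline information.

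On the stated rates and 278 analysed, the expected gain is about 0 to 3 power points. It grows somewhat if the true effect is smaller, which is possible. The planning rates ("a relapse rate of about 49% in the group that received surgery alone and 28.1% in the group that received surgery and GnRH agonist treatment") come from a study that the Discussion calls non-randomised. The authors' own retrospective data, also in the Discussion, showed no difference at one or two years, though they did at 36 months.

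These sizes rest on assumed prognostic strengths, because the article gives none. They also come from tests on the log-odds scale, not from the standardised risk difference recommended below.

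**What to change.** Before database lock, prespecify one primary covariate-adjusted analysis of 36-month relapse:

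- **Model.** Logistic regression on arm, focus size, age, and baseline pain and PBAC scores. Use only values recorded before the assignment is known, since the trial is open-label.
- **Estimate.** Standardise to a marginal risk difference with a 95% confidence interval. This keeps the scale the article already uses, a difference in recurrence rates.
- **Supportive.** Report the unadjusted Pearson chi-square alongside.
- **Hospital.** Handle it sparingly, by pooling small sites under a prespecified rule or by a Mantel-Haenszel sensitivity analysis. Fix the choice in advance, and do not enter nine separate indicators.
- **Route.** Include it only if the case report form records it.

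The cost is a change of wording and slightly more analysis work. No new data are needed for the covariates named, and the loss of power if they are not prognostic is negligible.

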### Outcome and outcome assessments

The primary outcome is relapse, which is defined as recurrence of dysmenorrhea or pelvic pain, or menorrhagia, or local recurrence compared to the first follow up after surgery as confirmed by 2D/3D-CDUS/MRI. Relapse as identified by 2D/3D-CDUS or MRI constitutes an increase > 1 cm in the maximal diameter of the suspected recrudescent focus during the follow-up period. The VRS and NRS are also applied for evaluation of dysmenorrhea or pelvic pain and the recurrence is defined as any increase in the scores and by participants asking for other medical treatments for relief of symptoms at the same time during follow up. The PBAC score is used to predict coagulation disorders in women with menorrhagia and recurrence is defined as a score > 100. The proportion of participants with recurrence at 3, 6, 9,12, 18, 24, 30, and 36 months will be recorded.

The secondary outcomes include quality of life, clinically confirmed pregnancy, ovarian reserve, and adverse events (AE). Quality of life is assessed by the SF-36 and FSFI, as measures of health status and sexual functioning in women. Ovarian reserve is evaluated by measuring FSH, E_2_, and AMH; the first two are measured before surgery and during the follow-up period at the beginning of the menstrual cycle unless the participant is currently receiving treatment with triptorelin acetate. AMH can be measured at any time before and after surgery at the time of follow up. Differences in scores for eight dimensions (physical functioning, role-physical, bodily pain, general health, vitality, social functioning, role emotional and mental health) of the SF-36 and for the FSFI, and the mean values of FSH, E_2_, and AMH for will be recorded for assessment of quality of life and ovarian reserve participants in each group of participants at 3, 6, 9,12, 18, 24, 30, and 36 months. The participant’s intention to become pregnant, the pregnancy rate, and outcome are recorded in a standard case report form, including details of abortion, premature delivery, and full-term delivery, to evaluate differences in pregnancy outcomes in each treatment arm at 36 months.

The follow-up procedure is acquired from the outpatient department records. Follow-up visits occur at 3, 6, 12, 18, 24, 30, and 36 months after conservative surgery.

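### Pregnancy rate and pregnancy outcomes are assigned to GEE or MMRM by time point, a method and target that suit these endpoints poorly and are not reconciled with the 36-month comparison in the outcome section

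*Protocol article*

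**What the plan says.** In the protocol article, the secondary-outcome paragraph under Data analysis plan lists the SF-36, the FSFI and the pregnancy endpoints together. It states that "the pregnancy rate, and pregnancy outcomes, are calculated during 36 months of follow up using GEE or MMRM analysis" and gives the purpose as "to compare groups A and B to identify differences between groups at different time points".

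The section Outcome and outcome assessments describes the same endpoints differently. The woman's "intention to become pregnant, the pregnancy rate, and outcome are recorded in a standard case report form". The purpose given there is "to evaluate differences in pregnancy outcomes in each treatment arm at 36 months". The results to be noted for each pregnancy are set out as "including details of abortion, premature delivery, and full-term delivery".

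Three other statements bear on the point:

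- The reason given for GEE or MMRM is "to account for correlation among these observations at different follow-up points". It is attached to pain scores, menstrual blood loss, and uterine and lesion size.
- The same plan assigns a Pearson chi-square test to categorical data and to the binary primary outcome at three years.
- Group B's injections start at the first menstruation after surgery, "then once every 4 weeks for six courses".

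**The concern.** This is not detail left to a later document. The article names both a method and a target for pregnancy, and both fit poorly.

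MMRM models a series of continuous values per patient. Pregnancy is binary. Abortion, premature delivery and full-term delivery are categorical results, known once per pregnancy and undefined for women who do not conceive, so they form no series of visit values for either model to use.

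The target is also unsettled. One section asks for a 36-month comparison and the other for differences by time point. The choice matters here because group B spends about the first six months on treatment, so early time points may show a delay in conception rather than a difference in fertility. The abstract and discussion both open with fertility preservation, so readers will look at this secondary result. If the model is not fixed beforehand, it could be chosen after the data are seen.

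**Working it through.** The documents give no pregnancy rate and no figure for this analysis, so there is nothing of the plan's own to reproduce. The check has four steps.

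**1. Match of method to data**

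| Endpoint | Type | Values per woman | MMRM | GEE |
|---|---|---|---|---|
| SF-36, FSFI | score | one per visit | suitable | suitable |
| Pregnancy by a given visit | yes/no, cumulative | one per visit, never reverting | not suitable | possible with a binomial link |
| Abortion, premature or full-term delivery | category | one per pregnancy, conceivers only | not suitable | no visit series to model |

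**2. Length of the treatment period**

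Six courses at 4-week intervals cover 6 × 4 = 24 weeks, or about 5.5 months, from the first menstruation after surgery. That is roughly the first six months. The 7-month delay to conception used in step 3 is an assumption, not a figure from the protocol.

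**3. What the permitted models would give**

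Inputs from the protocol: 308 women at 1:1, so 154 per arm, and the visit schedule "Follow-up visits occur at 3, 6, 12, 18, 24, 30, and 36 months after conservative surgery" (seven visits).

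Assumed: 30% of each arm pregnant by month 36, with conception times uniform over months 0–36 in group A and months 7–36 in group B. There is then no difference at month 36. Expected cumulative pregnancy is 30% × t/36 in A and 30% × (t − 7)/29 in B (zero before month 7):

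| Month | 3 | 6 | 12 | 18 | 24 | 30 | 36 |
|---|---|---|---|---|---|---|---|
| A (%) | 2.5 | 5.0 | 10.0 | 15.0 | 20.0 | 25.0 | 30.0 |
| B (%) | 0 | 0 | 5.2 | 11.4 | 17.6 | 23.8 | 30.0 |

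Averaged over the seven visits this is 107.5/7 = 15.4% against 87.9/7 = 12.6%. A single averaged arm effect therefore shows a gap that is absent at month 36.

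Simulation: 400 runs, binomial GEE on cumulative status, independence working correlation, visit effects plus one common arm effect.

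| Scenario | Chi-square at 36 months rejects | GEE with common arm effect rejects | Median odds ratio (GEE) |
|---|---|---|---|
| No delay | 4.5% | 3.8% | 1.01 |
| 7-month delay in B | 6.8% | 17.8% | 0.77 |

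Monte Carlo error, from √(p(1 − p)/400), is 1.9 points for 17.8% and 1.3 points for 6.8%. The chi-square figure is therefore compatible with 5%.

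In one simulated dataset with assumed true rates of 30% and 40%, a GEE with arm-by-visit terms gave a month-36 odds ratio of 1.328. The crude odds ratio was also 1.328 (p = 0.235 against 0.234 by chi-square). That form of GEE does not distort the 36-month result.

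**4. Delay remaining at 36 months**

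Assume instead an equal monthly conception chance f among women trying, starting in month 1 in A and month 7 in B. Cumulative conception is 1 − (1 − f)^(t − 1) in A and 1 − (1 − f)^(t − 7) in B.

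| f | Month 12, A v B | Gap | Month 36, A v B | Gap |
|---|---|---|---|---|
| 0.02 | 19.9% v 9.6% | 10.3 points | 50.7% v 44.3% | 6.4 points |
| 0.05 | 43.1% v 22.6% | 20.5 points | 83.4% v 77.4% | 6.0 points |

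A 36-month proportion reduces the built-in gap but does not remove it.

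**The case against.** The strongest reply is that the paragraph covers scores and binary outcomes together, so assigning GEE to the binary items is the natural reading. A logit GEE handles repeated binary status, and a stated interest in separate time points suggests visit-specific arm effects, the form that returns the crude 36-month contrast. This stands for the pregnancy rate: GEE as such is not the wrong tool. It does not rescue MMRM, and it does not help with delivery outcomes.

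A reader might infer that the two sections contradict each other. They do not. Month 36 is one of the time points, so the passages are unreconciled rather than incompatible.

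A reader might also infer that losses between visits would be missed, or a term pregnancy counted twice. That would need pregnancy to be coded as current status on the visit day, which the article never states. The case report form records pregnancies and their outcomes directly.

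It can fairly be said that delayed conception is a real consequence of assignment under intention to treat, and that step 4 shows it persisting in a 36-month proportion. Both are correct. The remedy is to label the delay, not to claim it has been removed. Finally, the absence of an analysis in women intending to conceive is the kind of detail a condensed article leaves out, and it is not held against the plan.

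**Conclusion.** The point holds as a badly fixed method for one secondary outcome. MMRM does not suit the pregnancy rate, neither named method suits the delivery outcomes, and the article does not say whether the by-visit or the 36-month contrast is the result.

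A reader might infer that the fertility result would be distorted. The documents do not support that: whether it is depends on visit coding and on common or visit-specific arm effects, which the article leaves open. What can be said is that the wording permits a model that could mislead. Its false-positive rate was about 18%, against about 7% for a 36-month chi-square. This rests on assumed 30% pregnancy in both arms, uniform conception times and a 7-month delay in group B. Without delay the two analyses behave alike. The primary outcome is not affected.

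**What to change.** - Keep GEE or MMRM for the SF-36 and FSFI.
- For pregnancy, use one record per woman: the proportion of randomised women with at least one clinical pregnancy by 36 months, compared between arms as a risk difference with 95% CI. This matches the outcome section and the plan's handling of its binary primary outcome.
- Show cumulative incidence of first pregnancy by arm as a description, stating that the early gap includes delay from group B's treatment period and that some may remain at month 36.
- Report full-term delivery per woman randomised. Tabulate abortion, premature delivery and full-term delivery per pregnancy as description only, because women who conceive are a group formed after randomisation.
- Add an analysis in women intending to conceive only if intention was recorded before randomisation. The article does not say when it is recorded, and Table 1 lists no such item at enrolment.

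The cost is analysis-plan wording, agreed before unblinding. Visit-specific contrasts for pregnancy are dropped, and any intention subset will be smaller, with a wider interval. If intention was not recorded before randomisation, that subset should be left out.
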